#### Attention Deficit / Hyperactivity-Disorder Rating Scale-IV-Preschool Version Translated

The ADHD RS-IV-Preschool Version has been translated into Danish for the purpose of the present study with permission from and formal approval by [name] (see Multimedia Appendix 1) according to international guidelines for the translation of questionnaires [47].

**Parenting Sense of Competence Scale**
* The Parenting Sense of Competence Scale (PSOC) [41] is the most frequently used questionnaire applied to measure parental self-efficacy and satisfaction [48]. It measures parental competence on two dimensions: Satisfaction and Efficacy. Separate scales are developed for mothers and fathers, who respond to 16 questions on a 6-point Likert-scale (ranging from strongly agree to strongly disagree) [1,6]. There are 9 questions that are related to Satisfaction and seven are related to Efficacy. The Satisfaction section examines parents’ anxiety, motivation, and frustration, while the Efficacy section looks at parents’ competence, capability levels, and problem-solving abilities in their parental role. A number of studies have demonstrated the scale’s good psychometric properties reporting internal consistency of .75 [41], and internal consistencies of .72 (mothers) and .76 (fathers) [48]. [name] gave permission and approval for the PSOC to be translated for the purpose of the present study (see Multimedia Appendix 4) according to international guidelines for the translation of questionnaires [47].

#### Strength and Difficulties Questionnaire Parent and Teacher Version

The Strength and Difficulties Questionnaire (SDQ) [39] is a brief behavioral five factor instrument developed to assess emotional and behavioral problems in children. The SDQ consists of 25 questions scored on a 3 point Likert scale (“not true”, “somewhat true”, “certainly true”). The questions cover five domains of child psychopathology by five subscales: hyperactivity/inattention, conduct problems, emotional symptoms, peer relationship problems, and prosocial behavior. Each area is covered by five questions. In addition, the SDQ contains an impact supplement inquiring about distress, burden, and impairment of the child. The questionnaire is widely used for clinical as well as research [49]. The standard SDQ is developed for use in the age-range of 4-17 years. The early years SDQ is developed for use in the age range of 2-4 years. A teacher version is developed for each scale, and a scale for completion by the young person is developed for use in the age range 11-17.

The SDQ has been used extensively in European as well as non-European contexts, and has been translated into more than 60 languages [50]. A recent review of the psychometric properties of the parent and teacher versions of the SDQ included 48 studies from 17 different cultural settings and a total of 131,223 raters [50]. The internal reliability and factor structure of the Danish versions of the SDQ were established in a sample of 71,840 parent and teacher raters of 5-, 7-, and 10- to 12-year-old children included in four large-scale Danish cohorts [51]. The predictive validity of the SDQ has been demonstrated in another large Danish study where the SDQ was shown to identify a group of children with highly increased risk of later being diagnosed and treated for ADHD or treated for ADHD in school age [52].

The early years SDQ—parent and teacher version Goodman [30]—has been translated into Danish for the purpose of the present study with personal permission and approval by [name] (see Multimedia Appendix 2) following standard guidelines for the translation of questionnaires [47]. The early years SDQ has shown good psychometric properties in a recent study [53].

*
**Family Strain Index**
*
The Family Strain Index (FSI) [42] is a 6-item parent-report questionnaire developed to assess the effects of ADHD on families to better understand and address the level of stress, strain, and burden that families experience. The FSI is designed to measure two major aspects of stress and demand, for example, the “emotional” and the “restrictiveness” experiences in the context of living with a child with ADHD. The FSI has demonstrated good internal consistency across the six items (Cronbach alpha= .83 to .87) and for the full scale (Cronbach alpha=.87) [42].

The FSI has been translated into Danish for the purpose of the present study (see Multimedia Appendix 3) following standard guidelines for the translation of questionnaires [47] with permission from and approval by the original developer [name].

#### The Adult Attention Deficit/Hyperactivity-Disorder Self-Report Scale

The Adult ADHD Self-Report Scale (ADRS-v1.1) is an 18-item Symptom Checklist covering the 18 DSM-IV-TR criteria for ADHD. The scale has been developed in conjunction with the World Health Organization (WHO), and the Workgroup on Adult ADHD [40]. The first 6 questions have been found most sensitive in the screening for ADHD in adults [54]. The 18-item scale has been translated into Danish and has been approved by the original investigators of the WHO Work Group. The scale provides a method of identifying ADHD symptoms in adults and is a powerful tool to discriminate DSM-IV cases from noncases [54]. The scale has good psychometric properties and is widely used in scientific research [55]. The validity and clinical feasibility of the Danish version of the ADHD-RS has been demonstrated in a multicenter study [56]. The measure will be used to evaluate the extent to which parental ADHD symptoms are associated to outcome [57].

#### The General Health Questionnaire

The General Health Questionnaire (GHQ) [44] is the most common assessment measure for assessing of mental well-being in adults. Developed as a screening tool to detect those likely to have or be at risk of developing psychiatric disorders, it is a measure of the common mental health problems/domains of depression, anxiety, somatic symptoms, and social withdrawal. It is available in a variety of versions using 12, 28, 30, or 60 items, which have all been translated into Danish. The present study will use the 12-item version GHQ:12. The measure will be used to evaluate the extent to which parental mental health is associated to outcome [58].

## Results

### Statistical Analysis

The data will be analyzed on an intention to treat basis. All outcomes will be analyzed with a repeated measure model with a randomization arm, gender, age (above or below 5 year), center, year, and a random level for each child as covariates. We will estimate the effect of the intervention at T2 (intervention, TAU) in terms of the difference between the change from T1-T2 and its effect at T3 in terms of change between the T3-T1. Missing data will be imputed assuming Missingness At Random in relevant analysis models including additional control variables if relevant. Outcomes with more than fifty percent missing will not be analyzed. To examine the effect of outliers, a sensitivity analysis will be performed excluding observation with residuals exceeding 2.5*SD. In addition, four other sensitivity analyses will be performed for each analysis exploring how sensitive the results are for reasonable deviations from the Missing At Random assumption. The missing data will be predicted based on the analysis of the observed data. In the first sensitivity analysis, we will reanalyze the data including the predicted value for the missing values, but add .2*SD to the missing data in the intervention group only. In the second sensitivity analysis, we will subtract .2*SD from the missing data in the intervention group only. In the third, we add .2*SD to the missing data in the TAU group only, and, in the last, subtract .2*SD from the missing data in the TAU group only.

The results for the primary outcome as a supplement will be split according to gender, single parenting (yes/no), oppositional defiant disorder/conduct disorder-comorbidity, and maternal ADHD symptoms. A number of scientific articles will be generated on the basis of collected data from this trial, including publications outlining moderator and mediator analyses. Results will be reported according to the CONSORT statement for nonpharmacological interventions [31].

**Time-Line** Funding for this trial was granted in 2011 and in 2014. Enrollment of participants started in August, 2012, and the data collection is expected to be finalized at the end of December, 2015. The primary outcome paper will be submitted for publication mid-year 2016.

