## Methods

### Trial Design

A randomized controlled trial will be carried out to investigate the effectiveness of the NFPP against a treatment as usual condition (TAU) in the treatment of ADHD in a clinical sample of young children referred to, assessed, and diagnosed at tertiary, preschool child psychiatry services in Denmark. The effectiveness of the NFPP intervention will be examined at three time points: T1 (baseline), T2 (week 12, post intervention), and T3 (6 month follow/up).

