### Eligibility Criteria

#### Inclusion Criteria

Inclusion criteria are: (1) child age between 3-7 years old; (2) child must have received a clinical diagnosis of ADHD, as informed by the Development and Well-Being Assessment (DAWBA) [4]; and (3) Danish must be first language spoken in the home.

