### Sample Size Estimation

The primary endpoint is parent ADHD ratings at T2. Sample size has been estimated at 126 children to obtain power at 0.80, ES=.50 (Cohen’s d). The usual convention that is generally proposed and accepted for randomized trials is that power in a study ought to be 0.80 when ES is estimated at 0.50 [33]. An estimated effect size of 0.5 is deemed reasonable for a trial evaluating the effect of parenting interventions in the treatment of ADHD. By comparison, a recent meta-analysis of parent training interventions for ADHD obtained an ES of 0.4 [34].

For a design comparing two groups, for example, NFPP versus TAU, and allowing for a participant drop out of 10%, a total of 140 children, for example, a sample of 70 children per group is needed to attain a power of 0.80 [35]. A drop out rate of 7% was reported in a Dutch parent training trial implemented in routine clinical CAMHS with a similar age group [36]. In this light, the present trial has chosen to operate with a potential drop out rate of 10%. The preschool child psychiatry sites at Risskov and Herning are expected to enroll 2/3 of participants and the Glostrup site is expected to enroll 1/3 of participants for the trial.

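### The single random child level gives the T2 and T3 change contrasts one pooled variance, so their standard errors can be misstated if the covariance over visits is not compound symmetric

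*Protocol article*

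**What the plan says.** The Statistical Analysis section sets one model for every outcome: "All outcomes will be analyzed with a repeated measure model with a randomization arm, gender, age (above or below 5 year), center", then year, "and a random level for each child as covariates". No other within-child dependence term is named. The section does not mention a residual covariance structure, a robust variance estimator or a degrees-of-freedom method.

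The treatment effect is defined through change from baseline at two visits: "in terms of the difference between the change from T1-T2 and its effect at T3 in terms of change between the T3-T1". Trial Design names three occasions: "T1 (baseline), T2 (week 12, post intervention), and T3 (6 month follow/up"). According to Sample Size Estimation, the primary endpoint is the parent ADHD rating at T2; the T3 effect is secondary.

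**The concern.** A random level per child with independent, equal-variance residuals makes all three visits equally variable and all pairs of visits equally correlated. With complete data the model then attaches the same standard error to the T2-T1 and T3-T1 contrasts, and the primary T2 standard error depends partly on how scores behave at T3.

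Two design features make equal difference variances doubtful:

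- T1-T3 is a longer interval than T1-T2, so its correlation may be lower.
- T1 precedes treatment while T2 and T3 both follow it, so T2 and T3 may be more alike than either is to T1.

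A standard error that is too small gives too many false positives and intervals that cover too rarely. One that is too large costs power. The model is prescribed for all outcomes, so the issue is not confined to one scale.

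**Working it through.** **The plan's own figure.** "Sample size has been estimated at 126 children to obtain power at 0.80", with a standardised difference of 0.50 ("An estimated effect size of 0.5 is deemed reasonable"). Alpha is not stated; 0.05 two-sided is assumed. Per arm, n = 2 × (1.96 + 0.84)² / 0.5² = 62.8, so 63, or 126 in total; 126 / 0.90 = 140. This reproduces the plan. (The exact t-test needs 128; power at 126 is 0.795.) The calculation is a plain two-group comparison with no covariance over visits, so it does not depend on the point below.

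**Formulas.** Take complete data, separate arm-by-visit means, one random child level and independent equal-variance residuals.

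- True variance of a within-child difference: v_jk = s_j² + s_k² − 2·r_jk·s_j·s_k.
- Variance the model uses for every difference: m = (v12 + v13 + v23) / 3.
- Ratio of model to true standard error: √(m / v12) at T2 and √(m / v13) at T3.
- Type I error: 2 × [1 − Φ(1.96 × ratio)].

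**Inputs.** The article gives no standard deviations or correlations over T1, T2 and T3. Its only related figure is the parent scale's test-retest reliability of .80 to .87, which is not a correlation between trial visits under treatment. All structures below are assumptions.

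| SDs at T1/T2/T3 | r12/r13/r23 | v12, v13, v23 | m | T2 ratio (type I) | T3 ratio (type I) |
|---|---|---|---|---|---|
| 1/1/1 | .60/.60/.60 | .80, .80, .80 | .80 | 1.00 (5.0%) | 1.00 (5.0%) |
| 1/1/1 | .60/.45/.65 | .80, 1.10, .70 | .867 | 1.04 (4.1%) | 0.89 (8.2%) |
| 1/1/1 | .60/.40/.60 | .80, 1.20, .80 | .933 | 1.08 (3.4%) | 0.88 (8.4%) |
| 1/1/1 | .70/.50/.70 | .60, 1.00, .60 | .733 | 1.11 (3.0%) | 0.86 (9.3%) |
| 1/1/1 | .70/.50/.60 | .60, 1.00, .80 | .80 | 1.15 (2.4%) | 0.89 (8.0%) |
| 1/1/1 | .50/.50/.70 | 1.00, 1.00, .60 | .867 | 0.93 (6.8%) | 0.93 (6.8%) |
| 1/1/1 | .50/.45/.75 | 1.00, 1.10, .50 | .867 | 0.93 (6.8%) | 0.89 (8.2%) |
| 1/1.3/1.3 | .40/.35/.75 | 1.65, 1.78, .845 | 1.425 | 0.93 (6.9%) | 0.89 (8.0%) |
| 1/1.3/1.3 | .50/.50/.50 | 1.39, 1.39, 1.69 | 1.49 | 1.04 (4.2%) | 1.04 (4.2%) |

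The pattern has a simple cause. T3-T1 tends to have the largest of the three difference variances, so averaging understates it. T2-T1 may lie above or below the mean, so its error has no fixed sign.

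**Checks.** In a REML fit to one simulated data set, the standard error was 0.1553 for both contrasts, the same as the formula gives. Simulation with 126 children and 20,000 runs gave type I error at T2 and T3 of 5.3% and 5.1% for .60/.60/.60, 3.4% and 8.2% for .60/.40/.60, 6.6% and 6.7% for .50/.50/.70, and 6.8% and 8.0% for .50/.45/.75.

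**Cost in power at T2.** In the .70/.50/.60 row, with a true difference of 0.5 and 63 per arm, the true standard error is √(2 × 0.6 / 63) = 0.138, so the expected z is 3.62. Power is Φ(3.62 − 1.96) ≈ 95% with the right standard error and Φ(3.62 − 1.96 × 1.155) ≈ 91% with the pooled one.

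**The case against.** The strongest reply is that nothing here is shown to be wrong. The article does not say that residuals are independent or equally variable, and it is a condensed account: a residual structure, robust variance or degrees-of-freedom method could well sit in the full plan. Even on the plain reading, equal difference variances make the standard errors exact, and no trial data are given to show inequality. This stands, and it makes the point conditional. It does not remove it, because the article does name a dependence term, names only that one, and applies it to all outcomes.

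It is also true that a model fitted to T1 and T2 alone contains a single difference, for which a random child level gives the right standard error. The article, however, describes one repeated-measures model yielding both contrasts and does not set the primary analysis apart.

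Three stronger readings are tempting, and the documents do not support them.

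- A reader might infer that entry by diagnosis ("child must have received a clinical diagnosis of ADHD, as informed by the Development and Well-Being Assessment") narrows the T1 spread and so makes the standard errors too small. Narrower T1 spread alone does the reverse: in the last row of the table they are about 3.5% too large. In the row above it they are too small because of the assumed T2-T3 correlation of .75. Entry is also by clinical diagnosis, not by a cut-off on the rating scale.
- A reader might take the visits to be clearly unequally spaced. The article does not say whether the 6 months run from baseline or from the end of treatment; if from baseline, the gaps are about 12 and 14 weeks. The argument needs only that T1-T3 is longer than T1-T2, which holds either way.
- A reader might add that a wrong covariance undermines likelihood-based handling of missing data. The article describes imputation under missing at random, with additional control variables where relevant and four shifted-value sensitivity analyses. No bias from this source has been quantified.

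**Conclusion.** The point holds as a conditional one. On its plain reading the stated model ties the T2 and T3 change contrasts to one pooled variance, an untested restriction that the design gives some reason to doubt. The error is modest at the primary T2 contrast and may run either way. At the secondary T3 contrast it is somewhat larger and usually anti-conservative: from 14% too small to about 3.5% too large in the structures tried.

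These figures rest on assumed correlations and standard deviations, complete data, a 5% two-sided test and the plain reading of the random child level. They illustrate the size and are not bounds. The documents do not support saying that the standard errors are wrong, only that they can be. The targets of 126 and 140 children stand.

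**What to change.** In the analysis plan, replace the single random child level with an unstructured within-child covariance over T1, T2 and T3, using Kenward-Roger or Satterthwaite degrees of freedom. Name the fallback in advance: if that model does not converge, use a simpler structure with robust standard errors. If a residual structure or robust variance is already planned, stating it would settle the point.

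The cost is one sentence and four more covariance parameters (six instead of two), which about 126 children at three fixed visits can support. Design, data collection and sample size do not change. If compound symmetry happens to be true, little is lost; if it is not, type I error returns to about 5% at both visits.

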**Results:**

The primary endpoint is change in ADHD symptoms as measured by the Preschool ADHD-Rating Scale (ADHD-RS) by T2. Secondary outcome measures include: effects on this measure at T3 and T2 and T3 measures of teacher reported Preschool ADHD-RS scores, parent and teacher rated scores on the Strength & Difficulties Questionnaire, direct observation of ADHD behaviors during Child’s Solo Play, observation of parent-child interaction, parent sense of competence, and family stress. Results will be reported using the standards set out in the Consolidated Standards of Reporting Trials Statement for Randomized Controlled Trials of nonpharmacological treatments.

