### Randomization Procedures

Since outcome may be dependent on treatment center and regional variations in referral pathways, as well as gender and age of the child, the study uses stratified allocation to treatment condition to ensure a balanced number of participants over conditions. Randomization is based on the defined strata as well as on the assigned treatment condition of earlier randomized participants within the strata. Parents will be randomized to one of the two arms using an allocation ratio of 1:1 for NFPP and TAU. Randomization to NFPP and TAU (1:1) will be generated by a Web-based randomization computer program within the Internet data management service Trialpartner [32], which allows for on-the-spot randomization of participants into an arm of the study. Randomization is done in blocks of size four or six and in 12 strata defined by center, gender, and age of the child (3-5 and 6-7 years). Once the parent has provided written informed consent to participate in the study, the administrator completes participant registration on the Internet in Trialpartner and enters a randomization request, at which point the randomization program randomly assigns the treatment condition, for example, NFPP or TAU, to the respective participant ID number. Trialpartner simultaneously generates an automated email message for the administrator and the main investigator of the study, in which participant ID, site, and treatment allocation is outlined. Parents are informed of their respective treatment condition following completion of the T1 visit, so that the first assessment is not influenced by participant’s knowledge of treatment condition. Information about treatment allocation is delivered to parents in a telephone call by the researcher who initially informed the parent of the study. 

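### The T2 effect is a change-score contrast without baseline adjustment, which loses precision, and it does not match the T2-rating comparison on which the sample size rests

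*Protocol article*

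**What the plan says.** The Statistical Analysis section uses one repeated-measures model for all outcomes, with a random level per child and with arm, gender, age, center and year as covariates. The T1 score is not in that list. The effect is defined as a contrast of changes: "We will estimate the effect of the intervention at T2 (intervention, TAU) in terms of the difference between the change from T1-T2". The T3 effect is defined in the same way.

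The endpoint is worded in two ways. The Abstract (Results) has a change: "The primary endpoint is change in ADHD symptoms as measured by the Preschool ADHD-Rating Scale (ADHD-RS) by T2". The Sample Size Estimation section has a level: "The primary endpoint is parent ADHD ratings at T2". That section continues: "Sample size has been estimated at 126 children to obtain power at 0.80, ES=.50 (Cohen’s d", and then adds dropout: "allowing for a participant drop out of 10%, a total of 140 children, for example, a sample of 70 children per group is needed". It names no SD for d and no T1-T2 correlation. For comparison it notes that "a recent meta-analysis of parent training interventions for ADHD obtained an ES of 0.4".

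Under Randomization Procedures, allocation is stratified by center, gender and age because outcome may depend on them.

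**The concern.** Two things look wrong.

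**Efficiency.** A difference in change subtracts the whole baseline score, whereas regression on baseline subtracts only the part that predicts T2. Regression is more precise at every r below 1. In addition, a covariate that is constant over time and enters only as a main effect adds the same amount to a child's T1 and T2 scores, so it cancels from the change. The strata were chosen because they may predict outcome, yet their adjustment would do almost nothing for the primary estimate.

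**Alignment.** The sample size describes a two-group comparison of T2 ratings, and the analysis tests change. These have the same variance only at r=0.5, so the power statement does not clearly describe the planned test.

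At stake is precision that costs no extra child or visit. It is worth having because the one effect size cited for comparison (0.4) is smaller than the 0.5 used for planning.

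**Working it through.** **Inputs.** From Sample Size Estimation: d=0.50, power 0.80, 126 evaluable children (63 per arm), 10% dropout, 140 randomised. From Randomization Procedures: 1:1 allocation. Assumptions: two-sided alpha 0.05 (not stated, but it reproduces 126, whereas one-sided 0.05 gives 100); equal SDs at T1 and T2; r is not given, so a range is shown.

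**Step 1: reproduce the plan's figure.** n per arm = 2(1.960+0.842)²/0.5² = 62.8, so 63, and 126 in total. 126/0.90 = 140. Power at 63 per arm = Φ(0.5·√(63/2) − 1.96) = Φ(0.846) = 0.801. The stated numbers reproduce. The t-test version gives 64 per arm, and power 0.795 at 63.

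**Step 2: variances, with the T2-score SD set to 1.** T2 comparison: 1. Change: 2(1−r). Baseline-adjusted: 1−r². Ratio of change to adjusted: 2(1−r)/[(1−r)(1+r)] = 2/(1+r).

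**Step 3: power at 63 per arm if d=0.50 is on the T2-score SD.** Power = Φ(2.806/SD − 1.96), where SD is the square root of the variance from step 2.

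| r | change variance | adjusted variance | ratio | change power | adjusted power |
|---|---|---|---|---|---|
| 0.3 | 1.40 | 0.91 | 1.54 | 0.660 | 0.837 |
| 0.4 | 1.20 | 0.84 | 1.43 | 0.726 | 0.865 |
| 0.5 | 1.00 | 0.75 | 1.33 | 0.801 | 0.900 |
| 0.6 | 0.80 | 0.64 | 1.25 | 0.881 | 0.939 |
| 0.7 | 0.60 | 0.51 | 1.18 | 0.952 | 0.976 |
| 0.8 | 0.40 | 0.36 | 1.11 | 0.993 | 0.997 |

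The T2-only comparison has power 0.801 in every row. The change contrast reaches 0.80 at r=0.498 with 126 evaluable, or at r=0.443 if all 140 are evaluable. Adjusted power never falls below 0.801.

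**Step 4: power if d=0.50 is on the change SD.** The change contrast has power 0.801 at any r. The adjusted comparison has standardised effect 0.5·√(2/(1+r)): 0.577 at r=0.5 (power 0.90) and 0.527 at r=0.8 (power 0.84). The efficiency gain therefore does not depend on which SD is meant.

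**Step 5: the strata covariates.** Random-intercept models with arm by visit were fitted to one simulated three-visit data set of 126 children at each r.

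- At r=0.5 with complete data, the T2 change contrast was −1.0634 (SE 0.180) both with and without gender, age and center main effects. It equalled the raw difference in mean change.
- With about 10% of children missing T2 and T3, it was −1.097 without and −1.094 with the covariates (SE 0.1878 and 0.1879). At r=0.3 the estimate moved a little more, from −0.435 to −0.461, with SE 0.216 in both.
- A model with a common T1 mean, fitted to the complete data, had SE 0.160 against 0.206 at r=0.3, 0.160 against 0.180 at r=0.5, and 0.102 against 0.107 at r=0.8.

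**The case against.** A reader might infer that the trial is underpowered, or that its 0.80 power holds only if r is about 0.5 or more. The protocol article does not support that. It does not say which SD d uses, and both the Abstract and the Statistical Analysis section speak of change; on the change SD, r drops out. Even on the T2-score SD, no T1-T2 correlation is given. The nearest figure is the parent-version test-retest reliability of .8 to .87. A 12-week correlation in a diagnosed, treated sample is likely to be lower, but nothing places it below 0.5.

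Nor is the baseline wasted. A change score uses it, and above r=0.5 it is more powerful than the T2-only comparison used for sizing. Under randomisation both estimators are valid, so this is a question of efficiency and not of bias. The inert covariates do not weaken the power statement either, because the sample size took no credit for them. Year is undefined; if it means year of measurement, it can vary within a child and need not cancel.

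Free T1 means are also an inference. The article writes out no arm-by-visit term, and a model with a common T1 mean could report the same contrast with most of the lost precision recovered. A condensed article may leave that to a fuller plan.

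All of this limits the point without removing it. The stated covariate list omits T1, the stated contrast is change, and the sizing section describes something else.

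**Conclusion.** The point holds as one of efficiency and alignment. On the natural reading of the Statistical Analysis section, the primary contrast has 1.54, 1.33 and 1.11 times the variance of a baseline-adjusted one at r = 0.3, 0.5 and 0.8. The adjustment for gender, age and center adds almost nothing to it: exactly nothing with complete data, and nearly nothing with dropout. This rests on T1 being an outcome with free arm means and on strata entering only as main effects.

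The power statement and the planned test are not aligned. Whether this costs power is undetermined: it depends on the unstated SD behind d and, if that is the T2-score SD, on an unstated r. A shortfall is possible at r below about 0.5 and is not demonstrated. The estimate remains valid throughout.

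**What to change.** 1. Analyse T2 and T3 with the T1 score as a covariate (T1 by visit), or use a constrained longitudinal model with a common T1 mean across arms.
2. Cross center, gender and age with visit, so that the adjustment acts on the T2 and T3 contrasts.
3. Use one definition of the primary endpoint in the Abstract, Sample Size Estimation and Statistical Analysis sections.
4. State the SD behind d=0.50 and the assumed r, and restate power for the contrast that will be tested. With d on the T2-score SD, baseline-adjusted power is about 0.80 or more at any r.

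The cost is analysis wording only, since parent ratings at T1 are already scheduled, provided that the change is made and documented before the data are unlocked. Timing needs checking. Data Management keeps the data locked until all participants have completed T3, but collection was expected to end in December 2015 and the article is dated April 2016. If the lock has already ended, the adjusted analysis should be labelled as added afterwards and reported beside the planned one.

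### As written, the four missing-data sensitivity analyses carry no imputation uncertainty and shift by only 0.2 SD, so they give falsely precise reassurance about a significant primary result

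*Protocol article*

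**What the plan says.** The Statistical Analysis section plans a repeated measures model with a random level per child, with missing data imputed under MAR. It then adds four sensitivity analyses whose stated purpose is "exploring how sensitive the results are for reasonable deviations from the Missing At Random assumption". Missing values are predicted from the analysis of the observed data. For the first analysis the instruction is "we will reanalyze the data including the predicted value for the missing values, but add .2*SD to the missing data", in the intervention arm only. The second subtracts 0.2 SD in the same arm, and the third and fourth do the same in the treatment-as-usual (TAU) arm. The section does not say which SD is meant, whether the prediction includes the child's random effect, or why 0.2 was chosen. For these four analyses it mentions no random draw, pooling or variance correction. Outcomes are still analysed with up to half of the values missing.

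The Sample Size Estimation section supplies the expected missingness: "Sample size has been estimated at 126 children to obtain power at 0.80", then "allowing for a participant drop out of 10%, a total of 140 children". Higher scores on the primary scale mean more symptoms, so for a result favouring NFPP the adverse analyses are the first (NFPP raised) and the fourth (TAU lowered).

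**The concern.** A sensitivity analysis for data missing not at random should be able to weaken a result when the missing children did worse than predicted. Two features work against that here.

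- **Precision.** A filled-in point that equals its prediction adds to the sample size but brings no residual scatter. The model sees a complete, less noisy data set and reports too small a standard error.
- **Size of shift.** A shift of 0.2 SD applied to a tenth of one arm hardly moves that arm's mean.

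The first can offset or exceed the second, so an analysis labelled adverse may give a stronger test than the primary one. These four analyses are the only stated check on departures from MAR, and they are to be run for each analysis. Readers would take an unchanged conclusion as evidence of robustness when the procedure could hardly have produced anything else.

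**Working it through.** **Inputs from the protocol article.** Effect size 0.5, power 0.80, 126 evaluable children, 10% dropout, 140 randomised 1:1 (70 per arm, 63 observed), shift 0.2 SD. **Assumed:** two-sided alpha 0.05 (not stated in the article); within-child correlation r = 0.5 unless noted; SD taken as the outcome SD.

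**1. The plan's own figure.** n per arm = 2 × (1.96 + 0.842)² / 0.5² = 62.8, so 63 per arm and 126 in total; 126 / 0.90 = 140. Both are reproduced.

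**2. Size of the shift.** Shift in the arm difference = missing fraction × 0.2 SD. With 63 observed per arm, SE = √(2/63) = 0.178 SD.

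| Missing per arm | Shift (SD) | SE = √(2/n observed) | Shift in SEs |
|---|---|---|---|
| 10% | 0.02 | 0.178 | 0.11 |
| 20% | 0.04 | √(2/56) = 0.189 | 0.21 |
| 30% | 0.06 | √(2/49) = 0.202 | 0.30 |

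**3. What this shift could do with a correct standard error.** At 10% missing, a result at z = 1.96 becomes 1.96 − 0.11 = 1.85, p = 0.065. Only primary results with p of about 0.038 to 0.050 could change. To overturn an observed difference of 0.5 SD, the one-arm shift would have to be (0.5 − 1.96 × SE) / missing fraction:

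- 10%: (0.5 − 0.349) / 0.10 = 1.5 SD
- 20%: (0.5 − 0.370) / 0.20 = 0.65 SD
- 30%: (0.5 − 0.396) / 0.30 = 0.35 SD

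**4. Standard error after filling.** The random-intercept model was simulated with 70 per arm, three visits and T2/T3 values missing. At 10% missing the observed-data SE is about 0.176. After filling, the model SE is about 0.162 (predictions with the child effect) or 0.166 (fixed effects only), while the true sampling SE stays at about 0.17-0.18. The ratios to the observed-data SE are about 0.92 and 0.94 at 10% missing, and 0.84 and 0.89 at 20%. With the child effect the ratio falls to 0.75 at 30% missing and 0.58 at 50%.

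The null rejection rate implied by an SE ratio k is 2Φ(−1.96k):

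- 10% missing: k = 0.94 gives 2Φ(−1.84) = 6.5%; k = 0.92 gives 2Φ(−1.80) = 7.1%
- 20% missing: k = 0.89 gives 2Φ(−1.74) = 8.1%; k = 0.84 gives 2Φ(−1.65) = 10.0%

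This agrees with the overall ranges of roughly 6.5-8% and 8-10%.

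**5. Shift and shrinkage together at 10% missing.** Adverse z = (z × 0.176 − 0.02) / filled SE. For a primary z of 1.96, the numerator is 0.345 − 0.02 = 0.325.

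- Child effect included: 0.325 / 0.162 = 2.01, larger than before. The adverse z exceeds the primary z whenever z > 0.02 / (0.176 − 0.162) = 1.4, which covers every significant result.
- Fixed effects only: 0.325 / 0.166 = 1.96, almost unchanged. The break-even is z = 0.02 / (0.176 − 0.166) = 2.0, and this kind of filling also perturbs the point estimate, so some results flip.

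**6. Significant primary results overturned by the adverse NFPP shift (simulation, true d = 0.4).**

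| Prediction | r | Missing | Overturned |
|---|---|---|---|
| Child effect | 0.5 | 10% | 0 of 1,271 |
| Fixed effects | 0.5 | 10% | 24 of 624 (4%) |
| Fixed effects | 0.7 | 10% | 36 of 831 (4%) |
| Fixed effects | 0.7 | 20% | 67 of 805 (8%) |

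At 10% missing the adverse z was larger than the primary z in all significant results with child-effect predictions. With fixed-effect predictions it was larger in 65% (r = 0.5) and 48% (r = 0.7).

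**The case against.** The strongest reply is that this is a journal article, and the number of draws and the pooling rule usually belong in an analysis plan that is not shown. The article does speak of imputation under MAR for the main analyses. That reply limits the point but does not remove it. For these four analyses the article states the recipe itself (predict, insert, shift, reanalyse), and the literal recipe is deterministic. If an analysis plan specifies multiple imputation here, the standard-error part falls away and only the small shift remains.

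A second reply is that a small shift under low dropout honestly reflects low dropout. With 10% missing, a modest departure from MAR really does move the estimate little, and 0.2 SD is 40% of the assumed effect (0.2 / 0.5). This partly stands. It is also why no particular grid of deltas can be called correct, and why one unexplained value tells less than a tipping point.

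Third, the lack of a scenario moving the arms in opposite directions matters little. The effects are close to additive, so the combined shift at 10% missing would be about 0.02 + 0.02 = 0.04 SD.

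A reader might go further and infer that these analyses can never overturn a result, that they would show robustness whatever the dropout mechanism, or that the adverse test is always the stronger one. The documents do not support this. They do not say which prediction is used; with fixed-effect predictions a few results flip, and the adverse z is larger in only about half to two thirds of cases. Nor does the lack of parent blinding raise the stakes here: biased rating and missing ratings are separate problems, and the article addresses the first with blinded observation and teacher ratings.

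**Conclusion.** The point holds and should be fixed. On the literal text the sensitivity standard errors are too small, by about 6-8% at 10% missing and 11-16% at 20%. The 0.2 SD shift at planned dropout is worth 0.11 standard errors. Together they make it rare for an adverse analysis to overturn a significant primary result, and with child-effect predictions they usually make the test statistic larger than in the primary analysis.

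The conclusion rests on reading the predicted value as a single deterministic value, on two-sided alpha 0.05, on an assumed correlation of 0.5 (0.5-0.7 for the overturn rates) and a true effect of 0.4 SD for those rates. If SD means the residual SD, the shift is smaller still.

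It would be wrong to infer that the primary estimate or its test is biased: neither is touched. The fault lies in supplementary analyses that would be reported with more reassurance than they can give, which is why it does not rank as a flaw in the trial's main conclusion.

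**What to change.** Run the shifted analyses by multiple imputation: proper draws under MAR, delta added to the imputed values in the chosen arm, the planned model fitted to each completed data set, and results pooled by Rubin's rules. State which SD defines delta. Extend the one-arm deltas beyond 0.2 SD until the primary conclusion changes, and report that tipping point so that readers can judge its plausibility. Shifting both arms in opposite directions is optional. If an analysis plan already specifies multiple imputation for these analyses, only the extension of the deltas is needed.

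The cost is a revised paragraph and a few hours of programming, with no new data and no design change. The sensitivity intervals will be wider.
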